### Criteria for discontinuing or modifying allocated interventions {11b}

Patients are free to withdraw from participation in the study at any time upon request, without any consequence. If a participant chooses to discontinue the study intervention, we will not collect or use their data.

LIPUS is an FDA-approved and safe treatment modality. To date, no adverse events have been reported with the low-power LIPUS regimen in soft tissue. Therefore, we anticipate that the risk to the safety of participants will be minimal. However, nursing staff will still monitor potential mild adverse reactions such as mild local swelling, spotting bleeding, enhanced local pain response, and local hyperesthesia or decrease. In case of corresponding symptoms, appropriate symptomatic treatment shall be carried out. Regardless, participants can withdraw from the study at any time if they experience adverse events that are unacceptable to them.

### Strategies to improve adherence to interventions {11c}

Lung CT examinations, ultrasound examinations, trial-related laboratory examinations, and relevant symptomatic treatment measures received by patients before and after treatment are provided free of charge to improve adherence to interventions.

### Relevant concomitant care permitted or prohibited during the trial {11d}

All participants will be given routine nutritional support care. We discourage additional treatments to that assigned (that is, not per protocol) during the intervention period. Participants will report all not-per-protocol treatments, such as adding antiviral agents.

### Provisions for post-trial care {30}

Trial interventions are designed to inflict minimal to no harm. If a participant suffers any injury due to participating in the trial, we will evaluate, document, and provide appropriate medical care and pay for all related medical expenses.

## Outcomes {12}

### Primary outcome

The primary outcome measure will be the difference in the extent of absorption and dissipation of lung inflammation on CT images. Result comparisons will be made between the test group and the control group and between the LIPUS-treated and non-treated areas within the self-control group.

Pulmonary inflammation on CT images will be assessed by an expert chest radiologist before and 7 days after treatment to compare the area and volume of inflammation in the target area of the lung, as well as the area absorption rate (AAR) or volume absorption rate (VAR). A Pair software will be used to mark and 3D reconstruct the target area of CT images and record the data of pulmonary inflammation changes. AAR is defined as [(target site inflammation area before treatment − target site inflammation area after treatment)/target site inflammation area before treatment] × 100 (%). VAR is defined as [(target site inflammation volume before treatment − target site inflammation volume after treatment)/target site inflammation volume before treatment] × 100 (%).

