Participants in the self-control group will be compared the LIPUS-treated area with the non-treated area in the lungs. First, a CT examination is performed to locate the body surface of the inflammatory exudative area. If the patient has bilateral pulmonary exudative inflammation, LIPUS treatment will be performed on one side of the lung, and the other will serve as the self-control group. Limited by the frequency of LIPUS, ultrasound cannot penetrate through one lung tissue to the other, and its maximum penetration depth is limited to the inside of the target lung. If the patient has unilateral pulmonary exudative inflammation, the inflammatory area will be divided into the upper and lower areas, and a single-area stimulus will be performed. The diameter of the two ultrasound probes is approximately equal to the width of the intercostal space, and the probes can be placed in the same intercostal space or in different intercostal spaces. The direction of sound beam can be adjusted manually. Limited by the width of the sound beam and the plane of sonication, the non-target inflammatory area above or below can be considered not to be affected.

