## Assignment of interventions: blinding

### Who will be blinded {17a}

Both patients and clinic staffs (caregivers, outcome assessors, and statistical analysts, etc.) will remain blind to group allocation. Whether the intervention is LIPUS-treated or non-stimulated will not be revealed throughout the study.

The clinician ([name]) who performed LIPUS therapy was not blinded to the grouping results and the course of treatment. The clinicians, [name] and [name], have access to the final trial dataset.

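### The primary CT outcome is read on the *target* area, which in the self-control group means the treated area, and the stated assessor blinding covers group but not clearly area

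*Protocol article*

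**What the plan says.** Primary outcome (Outcomes {12}) names two comparisons: test group against control group, and "between the LIPUS-treated and non-treated areas within the self-control group". On the reading it says: "Pulmonary inflammation on CT images will be assessed by an expert chest radiologist before and 7 days after treatment", the purpose being "to compare the area and volume of inflammation in the target area of the lung". It continues: "A Pair software will be used to mark and 3D reconstruct the target area of CT images". The first formula reads "AAR is defined as [(target site inflammation area before treatment − target site inflammation area after treatment)/target site inflammation area before treatment" and so on; VAR is the same with volume in place of area. Neither formula is given for an area that is not the target site.

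Intervention description {11a} sets up the self-control group. In bilateral disease, "LIPUS treatment will be performed on one side of the lung, and the other will serve as the self-control group". In unilateral disease the inflamed region is split into an upper and a lower part and one part is sonicated; of the other part it says that "the non-target inflammatory area above or below can be considered not to be affected".

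Who will be blinded {17a} states: "Both patients and clinic staffs (caregivers, outcome assessors, and statistical analysts, etc.) will remain blind to group allocation". Its next sentence undertakes that sonicated or unsonicated status will stay undisclosed for the whole study. The clinician who delivers LIPUS is named as unblinded.

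**The concern.** For the within-patient comparison, what has to be hidden from the CT reader is the area, not the group. Every self-control patient belongs to the same group, so a reader who is perfectly blind to allocation could still know which of two regions was sonicated. The protocol describes the reader's task in a word that, in this group, points to the sonicated region.

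Outlining a fading infiltrate is a matter of judgement. If the treated region is known, a small systematic difference in how tightly the two day-7 contours are drawn passes straight into AAR or VAR and looks like a LIPUS effect. Explanation for the choice of comparators {6b} gives the self-control group the job of removing between-patient differences, and the Discussion makes its verdict on efficacy depend partly on this group. A reader bias here would therefore reach the trial's conclusion.

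**Working it through.** **Step 1: what *target* means in the self-control group.** In {11a} the unsonicated part of a unilateral lesion is the non-target area. For bilateral disease the same section calls the lung that the beam enters the target lung. In both layouts the target is the treated region.

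**Step 2: what the reader handles.** Primary outcome puts the reading, the software marking and both formulas in terms of the target. The within-patient comparison also needs a measurement in the untreated region, for which AAR and VAR have no definition as written.

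**Step 3: what is masked.** Section {17a} promises blinding to group allocation. That is constant within the self-control group, so it gives no protection there. The non-disclosure sentence may extend to areas; if it does, it conflicts with a reading organised by target. No section says who places the mark, what label the reader sees, or whether the reader is kept from probe-position information. The secondary ultrasound outcome, by contrast, does carry its own masking statement: sonographers do not know the CT result.

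**Step 4: can the scan alone define the regions?** In bilateral disease, yes: left and right lung. In unilateral disease, no: the upper/lower division is set when treatment is planned, so someone must convey it, and the protocol does not say that this is done without revealing which part was treated.

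**Step 5: scale of a possible bias.** The protocol gives no figure for reader error or for the SD of AAR or VAR, so what follows is illustration. The number of self-control patients is 66/3 = 22 (Sample size {14}, before dropout), or 60/3 = 20 from the Abstract.

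*(a) From contour to VAR.* VAR = (before − after)/before × 100. Take before = 100 and true after = 50 in both areas, so true VAR is 50% in each. Assume the day-7 contour is 10% tight on the treated area and 10% wide on the untreated one:
- treated: after = 50 × 0.9 = 45, VAR = 55%
- untreated: after = 50 × 1.1 = 55, VAR = 45%
- false difference = 10 points

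If 10 points is the observed mean difference, the paired test is t = 10/(SD/√22) on 21 df:

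| Assumed SD of paired difference | t | two-sided p |
|---|---|---|
| 15 points | 3.13 | 0.005 |
| 20 points | 2.35 | 0.029 |
| 25 points | 1.88 | 0.075 |

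*(b) From bias to error rate.* Let b be the bias in SDs of the paired difference, with no true effect. The chance of a significant result is P(|T| > t₀.₉₇₅) for a noncentral t with n − 1 df and noncentrality b√n:

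| b | n = 22 | n = 20 |
|---|---|---|
| 0 | 5% | 5% |
| 0.1 | 7% | 7% |
| 0.2 | 15% | 14% |
| 0.3 | 27% | 25% |
| 0.5 | 61% | 57% |

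To link the two: with an SD of 20 points, the 10-point difference in (a) is b = 10/20 = 0.5. A contour error of 4% each way gives 52% against 48%, a difference of 4 points, so b = 4/20 = 0.2.

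**The case against.** A reader might infer that the radiologist must be told the treated area and that assessor blinding therefore fails. The documents do not go that far.

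- The marking sentence is passive. Another person could place the marks, or both areas could be marked under neutral codes.
- The non-disclosure sentence in {17a} can be read as covering areas. Its term for unsonicated is the one that the Abstract, Trial design {8} and {6b} use for the untreated area of the self-control group; the control group is described as receiving a null stimulus.
- *Target site* in the formulas could loosely mean the region being measured, since the rates must also be computed for controls, who receive no sonication, and for untreated areas.
- Two contours in one patient may reveal the arm, but not which area was treated.
- The unblinded clinician is not said to read CT.
- Reading logistics are often left to a fuller document than an article, and the bias sizes and SDs above are assumed.

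These points stand against any claim that blinding is broken. They do not remove the exposure. The looser sense of *target* is possible, but {11a} uses the word for the sonicated region, and the article fixes a target-labelled reading beside a promise of group blinding. If the non-disclosure sentence does cover areas, the sections need reconciling; if it does not, the area is unprotected. The point is therefore more than absent detail.

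The primary objective, LIPUS against control care, is not affected by this argument: if the target is the lesion under the worn probes in both groups, marking it does not show whether the stimulus was active.

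**Conclusion.** The concern holds as an exposure. For one of the two stated primary comparisons, the protocol words the CT reading so that the reader can learn which area was treated, and its explicit blinding to group does not address this. Whether any reader would in fact know, and how large the resulting bias would be, cannot be established from the document.

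The illustration shows only that modest bias would matter at this sample size: about 7% false-positive risk at 0.1 SD and about 61% at 0.5 SD with 22 patients, under a paired t-test, no true effect and an assumed bias that favours the treated area. One of the three worked p-values (SD 25 points) is not significant, so even the 10-point example does not always mislead. The matter should be settled before scans are read, because reads made with the treated area known cannot be fully repaired afterwards.

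**What to change.** **Primary outcome.** Have the existing radiologist segment all inflamed areas of both lungs in every patient of all three groups, on de-identified scans, without access to probe position or any target label. Lock the segmentations. The staff member who holds the allocation and probe-position records then assigns the treated and untreated regions. For unilateral self-control patients, use the upper/lower boundary recorded at baseline. No such division is needed in the other two groups, where {11a} defines none.

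**Formulas.** Define AAR and VAR for the treated and for the untreated area, so that the within-patient comparison has a defined outcome on both sides.

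**Who will be blinded {17a}.** State that assessor blinding covers the treated area as well as the group.

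**Cost.** More segmentation time for the same reader, and probe-position records filed apart from the images. No additional scan, reader or patient is required.

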### Sample size {14}

Sample size and power calculation are based on the primary outcomes. All sample size calculations assume two-sided analysis with a power of 90% (1-*β* = 0.90) at a significant level of *α* = 0.05. The use of therapeutic LIPUS in viral pneumonia has not yet been reported. Based on the time span of this clinical trial and the number of patients expected to meet the inclusion criteria in our hospital, it is estimated that a total of 66 participants will be required (1:1:1 allocation ratio). We anticipate minimal missing data (< 5%) for the primary outcome (day 7 pulmonary inflammation on CT images) because participants were all inpatients and we have daily contact with them during the treatment phase. With a dropout rate of approximately 5%, a final sample size of 70 participants is required.

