## Statistical methods

### Statistical methods for primary and secondary outcomes {20a}

Analysis of baseline characteristics of the three groups will be summarized by appropriate descriptive statistics. Analysis of both the primary and secondary outcomes will be performed blinded to treatment assignment and analyzed on the intention-to-treat approach [22], with all randomized participants retaining their original randomization group. If these missing data are judged to be random, multiple imputations of the chained equation will be used to address missing data caused by lost access and non-response.

Normally distributed data were expressed as the mean (standard deviation), whereas data not normally distributed was expressed as the median (interquartile range). The independent sample test was used for the comparison between groups, and the paired sample test was used for the comparison within the group before and after treatment. For clinical symptoms, variables were expressed as percentages. A *χ*^2^ test or Fisher’s exact test was used to compare categorical data. The conventional level of 0.05 for statistical significance was adopted to evaluate the *p*-values. Statistical analysis was carried out by using SPSS software, version 26.

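### The primary CT measure is left open and three sections disagree on the self-control comparison, so the primary result could be chosen after the data are seen

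*Protocol article*

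**What the plan says.** **Measure.** Outcomes {12}, Primary outcome, describes one concept, the resolution of inflammation on CT. It then calls for inflamed area and inflamed volume at the target site, at baseline and at day 7. To these it adds two derived rates: "as well as the area absorption rate (AAR) or volume absorption rate (VAR". AAR and VAR are each defined as percentage reduction from baseline. Neither is ranked above the other.

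**Comparison.** The same section states: "Result comparisons will be made between the test group and the control group and between the LIPUS-treated and non-treated areas within the self-control group". Neither comparison is called the main one.

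**Level.** Statistical methods {20a} says "The conventional level of 0.05 for statistical significance was adopted" and gives no order, split or adjustment. Sample size {14} says "Sample size and power calculation are based on the primary outcomes", in the plural, at a single alpha of 0.05. The missing-data section {20c} makes a sensitivity analysis depend on whether a primary test, in the singular, is significant. No section says which test that is.

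**Elsewhere.** The primary objective {7} is LIPUS against conventional care only. The choice of comparators {6b} describes the self-control arm as a way to remove differences between individuals. The Discussion grades LIPUS as effective, fair or poor by comparing the LIPUS group with the control group and with the self-control group.

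**The concern.** A protocol has to say which number decides the trial. Here the word joining AAR and VAR leaves that choice open, and the role of the self-control arm depends on the section one reads. An analyst who followed the text exactly could calculate both rates in both comparisons and report whichever reached 0.05 as the primary finding. Nothing in the text would be broken by doing so.

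Blinding does not close this route. Under {17b} the groups are revealed only after the primary and secondary analyses are complete, but a choice between measures needs only the p-values, not the group labels.

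At stake is whether a positive primary result in a trial of about 22 patients per arm can be taken at its nominal level.

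**Working it through.** **1. The plan's own figure.** Sample size {14} gives 66 participants at 1:1:1, two-sided 0.05 and 90% power, raised to 70 for 5% dropout.
- 66 / 0.95 = 69.5, rounded up to 70. This step reproduces.
- The 66 cannot be reproduced, because no effect size or SD is stated.
- Solved backwards, 22 per arm detects d = (1.960 + 1.282) × √(2/22) = 0.977 by the normal formula, or 1.00 by the t-test. That is the size for one measure in one two-arm comparison at 0.05. It contains no allowance for a second route to success.

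**2. The three accounts of the comparison.**

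| Section | Comparison(s) |
|---|---|
| Primary objective {7} | LIPUS vs control |
| Primary outcome {12} | LIPUS vs control; treated vs untreated area within self-control patients |
| Discussion | LIPUS group vs control group; LIPUS group vs self-control group |

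The Discussion's second comparison is between patients and is not the within-patient one in {12}. None of the three sections chooses between area, volume, AAR and VAR.

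**3. Chance of at least one false positive, each test at two-sided 0.05.** Significance in either direction is counted, so the benchmark is the nominal two-sided 5%.

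The two comparisons in {12} use different patients and are independent. For one measure: 1 − 0.95² = 0.0975.

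For several measures, the calculation simulated 200,000 trials with 22 patients per arm, using t-tests (two-sample for LIPUS vs control, one-sample on the within-patient difference for the self-control arm) and equally correlated measures. The Monte Carlo standard error is below 0.1 percentage point: √(0.16 × 0.84 / 200,000) = 0.0008. The correlations are assumptions; the protocol gives none.

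| What is left open | Correlation 0.95 | 0.8 | 0.5 | Independent |
|---|---|---|---|---|
| AAR or VAR, LIPUS vs control only | 6.5% | 7.9% | 9.2% | 9.75% |
| One measure, both comparisons | 9.75% | 9.75% | 9.75% | 9.75% |
| AAR or VAR, both comparisons | 12.6% | 15.3% | 17.5% | 18.5% |
| Area, volume, AAR, VAR, both comparisons (upper scenario) | 15.5% | 21.9% | 29.2% | 33.7% |

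The rows for both comparisons combine the two error rates as 1 − (1 − a)(1 − b). For AAR/VAR at 0.95: 1 − (1 − 0.0651)(1 − 0.0653) = 0.126. At 0.5: 1 − (1 − 0.0918)(1 − 0.0919) = 0.175.

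**The case against.** **The Discussion already ranks the comparisons.** Both of its favourable grades require LIPUS to beat control, and the primary objective names only that comparison. If that rule governed, the self-control arm would add no false-positive route, and only the first row of the table would apply. This is a serious point, and it is why the figures are given with and without the second comparison. It does not settle the matter. The rule sits in the Discussion, uses a different second comparison from {12}, gives no grade when only the treated-versus-untreated test is positive, and does not choose a measure.

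**The count of tests can be overstated.** A reader might infer eight primary tests, four measures in two comparisons, any one of which counts as success. The protocol does not say so. Area and volume are the inputs to AAR and VAR and may be meant only as that, so the last row of the table is an upper scenario.

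**No familywise promise is made.** A reader might also infer that the protocol guarantees 5% across all primary tests and breaks the guarantee. It does not: 0.05 appears as a sample-size input and as a conventional threshold for p-values. What stands is that the primary claim has no defined error rate until the primary test is named.

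**An analysis plan may settle it.** It could add an adjustment. Naming the primary measure, however, belongs in the protocol, and this text fixes it badly rather than leaving it out for brevity.

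**Conclusion.** The concern holds: the primary measure is unfixed, the role of the self-control comparison is inconsistent across {7}, {12} and the Discussion, and with no order or adjustment in {20a} the primary result can be selected after the data are seen.

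Over the assumed correlations of 0.5 to 0.95, the inflation runs from 6.5–9.2% (measure choice in LIPUS versus control only), through 9.75% (one measure, both comparisons), to 12.6–17.5% (AAR/VAR, both comparisons). The 15.5–29.2% scenario applies only if raw area and volume are also tested in both.

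No single multiple of 5% should be quoted. It depends on correlations the protocol does not give and on whether the self-control comparison can carry a claim alone. Area and volume of the same lesion on the same scan may correlate strongly, which would favour the lower ends. Every scenario exceeds 5%, and the defect itself does not depend on the exact figure. It should be fixed before analysis, because it decides what counts as a positive trial.

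**What to change.** - Name one primary measure before any group comparison is run, and so before unblinding. VAR is a natural choice because the target area is reconstructed in 3D; AAR would also do if fixed in advance.
- Name one primary comparison, LIPUS versus control as in the primary objective, at two-sided 0.05.
- Test the within-patient treated-versus-untreated difference in the self-control arm second, at 0.05, as confirmatory only if the first test is significant. This fixed sequence costs no alpha and does not change the sample size.
- Make the remaining CT measures secondary.
- Align the plural in Sample size {14}, the unidentified primary test in {20c} and the grading rule in the Discussion with this choice.

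Keeping the alternatives open would cost more. Under Bonferroni with an assumed standardized difference of 1.0, n per arm = 2(z₁₋α/₂ + 1.282)² rises from 22 to 25 for two tests (0.025 each) or 29 for four (0.0125 each). At 22 per arm, power by the normal formula falls from 91% to 86% or 79%.

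The cost is a wording amendment, with the ethics approval and trial-register report that {25} requires. Trial status puts recruitment at October 2022 to October 2023, so the amendment should be dated and should state that no outcome comparison had been seen. The downside is that the other CT measure and the within-patient result can no longer carry a positive claim alone.
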